### Evaluations

During the baseline measurement, the following descriptive characteristics will be collected: (i) gender, (II) age, (III) weight, (IV) height (V) dominant hand, (VI) current occupation, (VII) sport. In addition, the following information concerning the affected shoulder will be collected: (I) painful side, (II) duration of pain, (III) prior illness, (IV) taking medication. The chronology of the evaluation of the primary and secondary outcome measures is shown in Table 3.

**Table 3 Tab3:** Chronology of primary and secondary outcome measures

Results										
	Baseline Week 1	Week 2	Week 3	Week 4	Week 5	Week 6	1 week post	1 month post	3 months post	6 months post
Primary										
VAS	✔	✔	✔	✔	✔	✔	✔	✔	✔	✔
DASH	✔						✔	✔	✔	✔
Secondary										
Dynamometry	✔	✔					✔	✔	✔	✔
Goniometry	✔	✔					✔	✔	✔	✔
Algometry	✔	✔	✔				✔	✔	✔	✔

### Primary outcome measures

The main result of this study will be the intensity of shoulder pain measured by ***Visual Analogue Scale (VAS) for pain***. Participants will mark the intensity of their pain on the VAS, consisting of a 100-mm long horizontal line, which is anchored by the classifications of “no pain” at the left end (score 0) and “worst pain imaginable” rightmost (score 10), asking to the participant for the most intense pain episode perceived meanwhile doing daily activity. The VAS has demonstrated the ability to detect changes in pain, establishing a minimal clinically significant difference at 13 mm [41, 42]. And in patients treated for rotator cuff disease a difference at 14 mm [43].

### Secondary outcome measures

***Disabilities of Arm, Shoulder and Hand (DASHe), Spanish version.*** It will be used to determine the disability rate related to shoulder pain. The DASHe is a self-administered questionnaire consisting of a central body of 30 items and 2 optional modules, each with 4 items, intended to measure the impact of injury of the upper limb by playing musical instruments and performing sport or work. Each item is scored 1 to 5, with increasing values depending on the severity of symptoms. The score of the items are summed to obtain a total score, which can range from 30 to 150 points, which is converted to a scale from 0 (best possible score) to 100 (worst possible score).Optional modules, if any, are scored separately by the same method. The limit to invalidate the DASHe questionnaire is 4 or more unanswered questions. DASHe questionnaire allows assessing the perceived disability for the patient to perform various activities, including activities of daily life and symptoms such as pain, stiffness and loss of strength [44]. The minimally significant clinical difference in the DASHe for musculoskeletal upper limb problems in adults is 10.2 [45].
***Pressure Pain Threshold (PPT).*** Performed with a pressure algometer (Baseline® 30 kg) on the point of greatest mechanical hyperalgesia of the patient’s shoulder, on the spinous process of C7 and on the area of greatest mechanical hyperalgesia of the tibialis anterior. PPT is defined as the amount of pressure applied on the point to be assessed until a painful sensation appears. Three measurements will be carried out and the average will be calculated, to be used for data analysis. 30 s rest will be left between measurements. C7 and tibialis anterior measurements will be used to determine the effect of the central modulation of shoulder pain [28, 46].It has been established that algometry is a highly reliable technique for PPT measurements when the examiners are well trained. Chesterton et al. [47] showed that changes of more than 17.39 N/cm2 (1.77 kg/cm2) can be considered with certainty to represent real change. Algometry has been used to measure the impact of manual therapy on the treatment of trigger points in cases of shoulder pain with a one month follow-up [28].
***Shoulder range of motion***. It will be measured with a standard 18 cm plastic goniometer (Sammons Preston-Rolyan®). The following shoulder movements will be measured: flexion, extension, internal rotation, external rotation and abduction to end range without pain. Each movement will be measured three times, of which the average will be calculated, to be used in the analysis.The universal goniometer has shown good intraobserver reliability (intraclass correlation coefficient from 0.91 to 0.99), if consistent benchmarks are used [34], for flexion, extension, abduction and rotation [48]. A change of 6° to 11° is needed to be certain that there has been a real change in the goniometric measurements of the shoulder [34].Flexion will be measured with the participant in a sitting position with a strap around the abdomen and the back of the chair to limit trunk compensation. The goniometer axis will be aligned with the centre of the joint axis (inferior and lateral to the acromion). The fixed arm of the goniometer will follow the line of the trunk, and the mobile arm, parallel to the longitudinal axis of the humerus and it proceeds to actively raise the arm in the sagittal plane; with the thumb pointing upwards [34].For the extension movement, the participant will be placed prone; with the shoulder in the neutral position, elbow flexed 90° and the forearm in the neutral position. The goniometer axis will be placed at the midpoint of the lateral aspect of the glenohumeral joint. The fixed arm will be placed parallel to the patient’s trunk, and the mobile arm, parallel to the longitudinal axis of the humerus. And finally the arm will be actively extended in the sagittal plane [34].For the abduction movement, the participant will be placed in a sitting position with a strap around the abdomen and the back of the chair to limit trunk compensation. The goniometer axis will be located at the midpoint of the posterior side of the glenohumeral joint. The fixed arm will be placed parallel to the trunk, and the mobile arm, parallel to the longitudinal axis of the humerus. And finally the arm will be actively abducted in the frontal plane, with the thumb pointing upwards to allow the necessary external rotation [34].As for the internal rotation movement, it will be performed with the participant prone; 90° shoulder abduction, 90° elbow flexion and forearm in the neutral position. To avoid compensation, the thumb will be placed on the coracoid exerting pressure and the other fingers on the spine of the scapula, to control scapular rise. The goniometer axis will be aligned with the elbow olecranon. The fixed arm will stand upright, vertical to the floor and the mobile arm of the goniometer will be aligned along the midline of the forearm. Finally performing internal rotation [34].External rotation will be performed with the participant supine; hips and knees bent at 45°, 90° shoulder abduction, 90° elbow flexion and forearm in neutral. The goniometer axis will be aligned with the elbow olecranon. The fixed arm vertical to the floor and the mobile arm of the goniometer aligned along the midline of the forearm, finally performing external rotation [34].
***Strength in shoulder movements***. It will be measured with a hand dynamometer (microFET2® Hoggan Scientific LLC). The measurements will be taken in pounds and converted to kilograms-force. Strength in the following movements will be measured: flexion, abduction, external rotation and internal rotation.For measurements of isometric force in ER (external rotation) and IR (internal rotation), it has been found that the intraclass correlation coefficient (ICC) is 0.93 to 0.99. The minimum detectable change varies from 7.87 N (External Rotation) to 22.11 N (Internal Rotation) [48].The physiotherapist should stabilize manually or with straps the upper arm, shoulder, scapula and trunk, while performing the tests.Measuring the strength in flexion will be conducted with the participant in a sitting position with the shoulder at 45° of flexion and the elbow extended; the Dynamometer will be placed above the lateral epicondyle. The trunk will be strapped to avoid compensation [49]. Abduction will be carried out with the participant in a sitting position with 90° shoulder abduction, 90° elbow flexion and forearm neutral, positioning the dynamometer just proximal to the lateral epicondyle [50].Measurement of the internal rotation will be carried out with the participant supine; shoulder abduction, 90° elbow flexion and forearm neutral. The dynamometer will rest on the ventral side of the forearm, 2 cm proximal to the styloid process [48].For the measurement of external rotation, the participant supine; 90° shoulder abduction, 90° elbow flexion and forearm neutral. The dynamometer will rest on the back of the forearm, 2 cm proximal to the styloid process [48].While performing the baseline measurement, data for secondary outcome measures of the participant’s healthy side will also be collected in order to establish whether there is a baseline difference between the two sides before starting the intervention.

### Physiotherapist training

For the assessment and treatment, a series of training stages prior to starting the study will be implemented, intended to protocolize the actions carried out in the study. In these training stages, treatment techniques and measuring will be practiced in order to reach a consensus among the physiotherapists involved. Moreover, an external observer will value similarities of interventions between physiotherapists.

### Statistical analysis

Data analysis will be carried out following the evaluation standards of the design of experimental studies with a control group. The experimental group (dry needling + manual physiotherapy and therapeutic exercise) will be compared with the control group (sham dry needling + manual physiotherapy and therapeutic exercise).

Data will be analysed using SPSS v.22 software for Windows. All statistical tests will be carried out considering a confidence interval of 95% (*p*-value <0.05) to determine the effectiveness of the 2 interventions by the method of intention to treat. Prior to statistical comparisons, all data will be analysed to determine the distribution of normality by the Shapiro-Wilk test. Subsequently, the homogeneity of the two intervention groups will be studied using Student’s t test for independent samples for data conforming to normal and the Mann-Whitney test for data that do not. The sex variable will be studied through Pearson χ2 or Fisher’s exact test, if the former cannot be used. Then a descriptive analysis of the data for the dependent variables will be performed. In these analyses, the mean and standard deviation (SD) for the dependent variables with normal distribution will be calculated. For variables that do not conform to normal, the data will be expressed with the median and first and third quartiles.

For the sex variable, frequencies are used. The existence of differences within each group will be determined, taking into account each group in isolation, between the different measurements (baseline and one week after dry needling; and post-treatment: at one week, at one month, at 3 months and at 6 months) in each of the study variables. In the VAS variable, measurements will also be taken in the treatment sessions; 2nd week, 3rd week, 4th week, 5th week, 6th week, using ANOVA for repeated measures, supplemented with simple and Helmert-type contrasts for variables that follow normal or Friedman’s ANOVA test, supplemented by Dunn’s multiple comparison test for those variables that will not conform to normal. ANCOVA will be performed to see the effect through different analyzes of the results and to intensify statistical power of the study. For this, the existence of a linear relationship and the homogeneity between the crude and basal scores of the dependent variables will be previously studied.

For comparison between groups, a variable that we define as “difference” will be found; for each dependent variable, by subtracting the baseline measurement - at one week following needling, baseline - post 1 week, baseline - post 1 month, baseline - post 3 months and baseline - post 6 months (for the DASHe variable, the measurement will not be collected at one week after needling).

For the VAS variable, the “difference” variables will be found between baseline - week 2, week 3, week 4, week 5, week 6. To determine differences in dependent variables between the two intervention groups, the Student t test will be applied for related samples in variables whose data follow normal, in this case the effect size will be calculated according to the formula d = 2 t/√g. In the case of variables whose data do not follow normal, an analysis by the Mann-Whitney test will be performed and the effect size will be estimated according to Grissom procedures according to the formula.

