Treatment of shoulder pain usually begins with conservative therapies such as rest, physical therapy, anti-inflammatory drugs (NSAIDs) and corticosteroid injections [15, 16]. However, current studies have shown the benefits of a multimodal treatment for shoulder pain including techniques such as dry needling, stretching, manual therapy, mobilization techniques, applying cold, home exercise, ischemic compression of MTrPs and ergonomic recommendations [1, 17].

The choice of treatment is often subjective and depends on the therapist’s skill and training, while therapeutic exercise programmes in combination with manual therapy techniques often show good results [5, 18]. A recent meta-analysis by Kietrys et al. [5] recommends using dry needling, compared against placebo, to reduce pain, following treatment, and at 4 weeks follow-up in patients with Myofascial Pain Syndrome of the Upper Quadrant. However, new studies to support this recommendation are required.

It has been suggested that the inclusion of dry needling, in a single session, within a multimodal physiotherapy programme for patients with post-surgery shoulder pain, produces improvements in on and range of motion [19]. However, we have not found similar studies in patients with chronic shoulder pain of unspecific origin.

Therefore, the main aim of this study is to determine the effectiveness of including dry needling in a manual physiotherapy and therapeutic exercise programme, for the treatment of chronic shoulder pain of unspecific origin. Our hypothesis is that by including a single session of dry needling in a manual physiotherapy and therapeutic exercise programme, treatment outcomes improve, reducing symptoms and improving function in patients with shoulder pain.

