### Sample size

The pain variable is chosen as the primary measurement of the study results. An effect size TE = 0.25 will be considered [21]. A correlation between repeated measures of 0.5 shall be assumed. Assuming the performance of 6 measurements -basal and a week after the dry needling, and post-treatment: at one week, at one month, at 3 months and at 6 months- in two treatment groups, sphericity correction will be determined at 0.5. With a statistical power of 0.95, with an alpha level of 0.05, a total sample size of 28 patients is estimated, and taking into account 25% for losses, a total of 36 patients needs to be reached, being 18 in both groups, using the Software Gpower 3.0.18 [22].

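### Effectiveness is to be judged at unadjusted p<0.05 across 64 between-arm secondary tests, and no single measure and visit decides the function claim

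*Protocol article*

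**What the plan says.** The Background section hypothesises that with one needling session added, "treatment outcomes improve, reducing symptoms and improving function in patients with shoulder pain". Pain has a named main outcome. Under Primary outcome measures, "The main result of this study will be the intensity of shoulder pain measured by" the VAS.

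The Secondary outcome measures section then lists:
- DASHe, one score (plus optional modules).
- Pressure pain threshold at three sites: the shoulder, C7 and tibialis anterior. On the two remote sites it says "C7 and tibialis anterior measurements will be used to determine the effect of the central modulation of shoulder pain".
- Range of motion in five movements: "flexion, extension, internal rotation, external rotation and abduction to end range without pain".
- Strength in four movements: "Strength in the following movements will be measured: flexion, abduction, external rotation and internal rotation".

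Table 3 differs in one respect: it places DASH under Primary, beside VAS.

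The Statistical analysis section defines the between-arm comparison as a change score, formed "for each dependent variable, by subtracting the baseline measurement - at one week following needling, baseline - post 1 week, baseline - post 1 month", and then at 3 and 6 months. That makes five change scores per measure, or four for DASHe, which is not collected one week after needling. The same section sets the significance rule: "All statistical tests will be carried out considering a confidence interval of 95% (*p*-value <0.05) to determine the effectiveness of the 2 interventions". The only multiple-comparison procedure it names, Dunn's test, supplements the within-group Friedman analysis. It does not touch the comparisons between arms. ANCOVA is announced as a further analysis.

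**The concern.** The hypothesis has two parts, symptoms and function. The symptom part has a named outcome. The function part has none: DASHe, any of five ranges of motion or any of four strength measures, at any of four or five visits, could be put forward as its test. The significance rule gives each of them the same standing at 0.05, with effectiveness as the stated purpose.

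An author who followed the text exactly could report improved function on the strength of, say, one movement at one visit, and nothing in the plan would mark that as a chance finding. The remote pain thresholds raise a similar but smaller problem for a statement about central modulation. What is at stake is the credibility of the function and pain-sensitivity conclusions.

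**Working it through.** The plan states no familywise error rate, so there is no figure of its own to reproduce. Its only relevant figure is 0.05 per test.

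**Step 1: count the tests** (Secondary outcome measures; change scores from Statistical analysis).

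| Domain | Measures | Change scores each | Tests |
|---|---|---|---|
| DASHe | 1 | 4 | 4 |
| Pressure pain threshold | 3 | 5 | 15 |
| Range of motion | 5 | 5 | 25 |
| Strength | 4 | 5 | 20 |
| Total | 13 | | 64 |

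Function subset: 4 + 25 + 20 = 49. If DASH is primary, as in Table 3: 64 − 4 = 60 tests on 12 measures. The count leaves out the optional DASHe modules, the week-3 algometry in Table 3 and all within-group tests.

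**Step 2: expected false positives under no treatment effect.** These do not depend on correlation: 64 × 0.05 = 3.2 in either direction. Sidedness is not stated. I take the tests as two-sided, so each has a 0.025 chance of falsely favouring needling, and 64 × 0.025 = 1.6.

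**Step 3: upper reference, independent tests.** Either direction: 1 − 0.95^64 = 0.962. Favouring needling: 1 − 0.975^64 = 0.802. With 60 tests these are 0.954 and 0.781.

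**Step 4: allow for correlation.** The tests are not independent, so the chance of at least one p<0.05 was simulated: null treatment, 18 per arm, two-sided t tests on change scores.
- Visit correlation: 0.5, from the Sample size section. Two change scores sharing a baseline then have covariance 0.5 − 0.5 − 0.5 + 1 = 0.5 and variance 2(1 − 0.5) = 1, so they correlate at 0.5.
- Between-measure correlation: not in the document, so it is an assumption and is varied.

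| Between-measure correlation | Any of 64, either direction | Any of 64, favouring needling | Any of 49 function tests, favouring needling |
|---|---|---|---|
| 0 | 0.93 | 0.71 | 0.61 |
| 0.5 | 0.80 | 0.46 | 0.41 |
| 0.9 | 0.45 | 0.23 | 0.22 |

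With 4,000 trials the standard error near 0.46 is √(0.46 × 0.54 / 4,000) ≈ 0.008.

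**Step 5: sensitivity.** A second set of runs used correlation 0.5 within a domain and 0.3 across domains.
- Base case: 0.86 in either direction, 0.53 favouring needling.
- 14 per arm instead of 18: 0.87 and 0.53. The sample size does not drive the result.
- Visit correlation 0.7: 0.87 and 0.54.
- Paired t test, as the Statistical analysis section words it: 0.86 and 0.54.
- Either the t test or the ANCOVA may count: 0.96 and 0.68.

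**Step 6: compare with nominal.** Favouring needling, 0.46 / 0.025 ≈ 18 times at correlation 0.5, and 0.23 / 0.025 ≈ 9 times at 0.9. For the function tests, 0.41 / 0.025 ≈ 16 times.

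**The case against.** The best defence is that these outcomes are labelled secondary, one main outcome is named, and unadjusted secondary tests beside a named primary are common. The significance sentence can be read as a general statement of level, and nowhere does the article say that one significant secondary result establishes effectiveness. A hierarchy or an exploratory label may sit in an analysis plan that is not shown. The Discussion restates the aim as reducing pain and disability, and disability is what DASHe measures, so the document leans towards DASHe as the function outcome.

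Part of this stands. The absence of a hierarchy would not be a finding by itself, and the family of 49 is a grouping made here from the hypothesis, not one the article defines. The wording about central modulation mostly explains why remote sites are measured and is a minor matter. What does not fall away is that the article goes beyond silence. It fixes 0.05 for all tests, attaches effectiveness to them, and puts function in the hypothesis. Leaning towards DASHe still leaves four visits with none chosen, and a label that differs between Table 3 and the outcome section.

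Three stronger readings are tempting but unsupported:
- A reader might infer that a useless treatment would very likely yield a false claim for needling. That confuses either-direction significance with a favourable result. The favourable chance is about 0.46 at correlation 0.5 and passes one half only at lower correlations.
- A reader might blame the small sample. The rate is the same at 14 and 18 per arm.
- A reader might think the main pain conclusion is compromised. These 64 tests do not include VAS.

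**Conclusion.** The point holds, limited to claims on function and pain sensitivity. The count of 64 (or 60) follows directly from the article. Under no effect, a favourable false positive somewhere among these tests has a chance of roughly one in four to seven in ten, depending on how strongly the measures correlate. Within the function tests it is roughly one in five to six in ten. Even the lowest of these figures is about nine times the nominal 0.025 (0.22 / 0.025 = 8.8).

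The size rests on three assumptions: two-sided tests, a visit correlation of 0.5 carried over from the pain calculation to the other measures, and a between-measure correlation the document does not give. The conclusion survives the whole range examined; the exact figure does not. This should be corrected before the data are analysed, but it does not undermine the trial's main comparison.

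**What to change.** 1. Reconcile the status of DASH between Table 3 and the Secondary outcome measures section. This decides which tests belong to the secondary family.
2. In Statistical analysis, name the between-arm DASHe difference at one pre-stated visit as the single test of the function claim.
3. Decide whether that test stands alone or follows VAS in a hierarchy. The hierarchy is a choice, not a necessity. If it is used, one VAS visit must also be named as primary, because VAS is compared at many visits and none is singled out, so a gate could not otherwise be applied.
4. Label every other secondary comparison exploratory: pressure pain threshold at all sites, each range-of-motion and strength movement, and DASHe at the remaining visits. Report them as between-arm differences with 95% confidence intervals.
5. Restrict the effectiveness wording of the significance rule to the pre-named tests.

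The cost is a change of wording, with no new patients or data. The one loss is that an isolated significant result on range of motion, strength or pain threshold can no longer be presented as proof of effect.

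### The between-group rule is a raw change score with a test picked by a normality pre-test, while the planned ANCOVA has no stated role; a baseline-adjusted comparison should be named primary

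*Protocol article*

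**What the plan says.** All references are to the protocol article.

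- **Principle.** Statistical analysis states that the tests are meant "to determine the effectiveness of the 2 interventions by the method of intention to treat".
- **Pre-test.** Before any comparison, "all data will be analysed to determine the distribution of normality by the Shapiro-Wilk test". The result decides between parametric and rank methods throughout.
- **Within each arm.** Change over time is examined separately in each group, "using ANOVA for repeated measures, supplemented with simple and Helmert-type contrasts for variables that follow normal", with Friedman and Dunn tests otherwise.
- **ANCOVA.** "ANCOVA will be performed to see the effect through different analyzes of the results", and to increase power, after checks of linearity and homogeneity against the baseline scores. Neither the visit nor its standing against the other analyses is given.
- **Between arms.** The last two paragraphs of the section define, for each outcome, the difference between baseline and each later measurement. These differences are compared by a t test if normal and by Mann-Whitney if not, with a different effect-size measure for each.
- **Design inputs.** Sample size assumes a correlation of 0.5 between repeated measures and reaches 36 patients, 18 per arm, "taking into account 25% for losses".

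**The concern.** Two different treatment comparisons are planned, change score and ANCOVA, and neither is ranked above the other. If they disagree, the choice can be made after the results are known.

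The one set out in operational detail is the less efficient. Subtracting baseline amounts to fixing the regression slope of follow-up on baseline at 1. When the true slope is about 0.5, as the assumed correlation implies with equal SDs, this adds as much noise as it removes. With 36 patients, precision given up at the analysis stage is costly.

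The normality pre-test adds a further choice. It lets VAS be reported as a mean difference at one visit and a rank comparison at the next, so what is being estimated is not settled beforehand.

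**Working it through.** **Inputs.** Correlation ρ = 0.5 and 18 per arm (Sample size). Smallest clinically relevant VAS difference 13 mm (Primary outcome measures). Two-sided 5% test, from "with an alpha level of 0.05"; two-sidedness is my assumption. Also assumed: equal SDs σ at baseline and follow-up, and σ = 15, 20 or 25 mm, since the protocol gives none. The between-arm t test is taken as the independent-samples form. The protocol words it as the related-samples form, which cannot apply to two separate groups and needs its own correction.

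**The plan's own figure.** The sample size uses "An effect size TE = 0.25 will be considered" (read as Cohen's f) and "With a statistical power of 0.95" for a repeated-measures ANOVA with six measurements. By noncentral F, 28 patients give 95.4% power with no sphericity correction. With the stated correction of 0.5 they give 78.5%, and 46 are needed. That is a separate matter; the comparison below takes 18 per arm as given.

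**Step 1: variance per patient, in units of σ².**

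- Follow-up score alone: 1
- Change score: 2(1 − ρ)
- Baseline-adjusted: 1 − ρ²

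| ρ | Change | Adjusted | Reduction |
|---|---|---|---|
| 0.3 | 1.40 | 0.91 | 35% |
| 0.5 | 1.00 | 0.75 | 25% |
| 0.7 | 0.60 | 0.51 | 15% |

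At ρ = 0.5 the change score has exactly the variance of the follow-up score alone. Adjustment is worth 1/0.75 = 1.33 times the patients: 36 × 0.75 = 27 patients analysed with adjustment match 36 analysed by change score.

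**Step 2: power for 13 mm at one visit, ρ = 0.5, 18 per arm.** Noncentral t, with standardised effect 13/σ for change and (13/σ)/√0.75 for adjustment.

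| Assumed SD | Effect, change | Effect, adjusted | Power, change | Power, adjusted |
|---|---|---|---|---|
| 15 mm | 0.87 | 1.00 | 0.71 | 0.83 |
| 20 mm | 0.65 | 0.75 | 0.47 | 0.59 |
| 25 mm | 0.52 | 0.60 | 0.33 | 0.42 |

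With 14 per arm (28 in all, the size before the loss allowance) and SD 20 mm, power goes from 0.38 to 0.48. The formula ignores the small cost of estimating the slope. In simulation at 0.8 SD and 18 per arm, ANCOVA reached 75.3%, against 76.7% by formula.

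**Step 3: the pre-test.** The procedure was simulated with Shapiro-Wilk on the change scores in each arm and Mann-Whitney used if either arm fails; the protocol does not say on which values or in which groups the test is run.

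- Type I error of the two-stage procedure was 4.9% to 5.3% for normal and skewed data, so there is no material inflation.
- With normal data and 18 per arm, about 10% of datasets were still sent to the rank test. Table 3 implies nine VAS differences (weeks 2 to 6 and four post-treatment visits), so on average about 9 × 0.10 = 0.9 of them would switch measure by chance alone.
- At 0.8 SD with normal data, power was 64.5% for the two-stage procedure and 75.3% for ANCOVA.

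**The case against.** The best defence is that the protocol does plan ANCOVA, gives power as a reason, and attaches routine assumption checks. So it would be wrong to say that baseline is ignored. That stands. What it leaves open is which analysis decides: the paragraphs that define the between-group comparison do not mention ANCOVA.

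A reader might go further and infer that the stated methods cannot deliver intention to treat, because repeated-measures ANOVA and Friedman drop anyone with a missed visit. If each of nine VAS visits were missed by 3% of patients independently, 1 − 0.97⁹ = 24% would lack a complete record. The document does not support this, for three reasons:

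- Those methods are confined to change within each arm. The treatment comparison goes visit by visit and loses only patients absent at that visit, about 3% in the same scenario.
- The article is silent on missing values. Handling them may be left to a SAP that is not shown, and analysis by allocated group, with or without imputation, is compatible with every test named.
- The 25% is an allowance already built into the 36, not a decision to exclude a quarter of the patients.

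It is also fair that the gain depends on ρ and that the power figures rest on an assumed SD. Adjustment had the lower variance at every ρ examined, however, and gave the higher power at every SD.

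**Conclusion.** The point holds as an unranked choice between two analyses, with the less efficient one set out as the between-group rule. At the protocol's own correlation, and with equal SDs, baseline adjustment reduces variance by 25% (15% to 35% for correlations from 0.7 down to 0.3) without any extra patients. For 13 mm with 18 per arm that is about 9 to 12 percentage points of power over SDs of 15 to 25 mm. Power stays modest at the larger SDs under either analysis, so this improves the trial but does not make good its size.

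The pre-test is a lesser fault: error control is not damaged, but the effect measure is not fixed in advance. No failure of intention to treat is established.

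**What to change.** Name one baseline-adjusted comparison as the primary between-arm analysis of VAS, and use the same method for the other outcomes. Either of two forms would do:

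1. The ANCOVA already planned, with arm and baseline value, at one named primary visit.
2. A linear mixed model with baseline, arm, visit and arm-by-visit, fitted to all available post-baseline data of all randomised patients, with one named primary contrast. With 36 patients it needs a restricted covariance structure or only the main visits: an unstructured matrix has 9 × 10/2 = 45 parameters for nine visits, against 5 × 6/2 = 15 for five.

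Judge normality on model residuals. Keep change scores and rank tests as sensitivity analyses, and remove Shapiro-Wilk as the rule that selects the test.

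The cost is wording, settled before the data are analysed; SPSS v.22 fits both models. Both assume a linear relation with baseline, which the protocol already intends to check. The mixed model also assumes data missing at random. It uses the earlier visits of patients who leave but does not recover their later values, so it is not a complete answer to missing data.
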